### Participants

Forty participants will be enrolled in the study. Eligibility of participants will be checked based on the following inclusion criteria: (a) adults aged 18–35 years; (b) to have a diagnosis of DD (ICD-10 code: F81.0) (World Health Organization, 1992) or a reading performance of at least 1.5 SD below the norm. Exclusion criteria include intellectual disability, psychiatric conditions, comorbidity with neurodevelopmental disorders (e.g., ADHD), neurological disorders, epilepsy, and enrollment in linguistic or literature university courses. Participants will be recruited by advertising the study through the Learning Disability services of two university campuses. Potential participants will have to provide demographic, clinical (i.e., psychiatric and neurological conditions), and educational information (i.e., years of education, field of study, average grades) and to complete a few self-report standardized questionnaires about their reading abilities. Potential participants who received a diagnosis of DD made by an independent clinician prior the enrollment in the investigation will be asked to share their clinical documentation with the researchers.

### Procedure

Participants who will respond to the recruitment advertisement will receive a detailed description of the experimental procedure and written informed consent to participate in the study *via* email. If they will provide their consent, participants will be asked to complete an online screening phase to check their eligibility. Eligible participants will be selected based on the inclusion and exclusion criteria of the study and will be randomly assigned to one of two experimental conditions (i.e., active NF training; sham NF training; and 1:1 ratio).

The study will include two experimental sessions: A preliminary screening session will be conducted to record EEG data of participants during resting state (i.e., eyes open 3-min) and two linguistic tasks (see section “Neurophysiological Measures”). This phase will provide information about EEG band variability. Data of participants who will have shown an abnormally low α frequency (i.e., α peak frequency below about 8.5 Hz at TP during resting-state), which could potentially make calculations on the β/θ ratio misleading, will be excluded from the analyses. EEG data collected during the screening phase will be elaborated; A measure of hemispheric asymmetry will be calculated (i.e., TP7–TP8) to (1) monitor whether and to what extent the degree of asymmetry in the ratio can influence the outcomes of the following training, and (2) to allocate participants equally to the experimental and the placebo conditions. Indeed, participants will be assigned to one of two experimental conditions (i.e., active NF training; sham NF training; and 1:1 ratio) using stratified randomization based on the β/θ asymmetry scores.

Thereafter, during the second experimental session (NF training), each participant will be asked to participate in one lab session of approximately 90 min, which will include seven phases: (1) pre-training behavioral assessment using standardized tests to measure reading, rapid automatized naming (RAN), and verbal working memory; (2) pre-training EEG recording as proposed in the screening session (resting state and the two linguistic tasks randomized to avoid familiarity effects; (3) NF warm-up (NF1; 10 min); (4) NF training (NF2; 20 min); (5) post-training behavioral assessment using the same tests of the pre-training phase; (6) NF reinforcement training (NF3; 10 min); and (7) post-training EEG recording. Time breaks will be provided to exclude excessive cognitive workload and fatigue during the procedure. Finally, to test the appropriateness of the blinding procedure, participants will be asked to judge their NF condition allocation, by reporting if they think they received either the sham or the active NF training.

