### Data Analyses

First, demographics and behavioral baseline assessment of experimental and control groups will be compared, to test any potential difference between groups for variables relevant to the aim of the study, together with the variables related to the asymmetry scores as described in section “Procedure”. Thereafter, a series of GLMs is intended to be carried out to compare the effect of the active NF training with those of the sham NF training. For doing that, a mixed factorial ANOVA 2 × 2, considering Phase (pre vs. post) and Condition (experimental vs. sham) as the independent variables will be carried out for each dependent measure (i.e., separate left and right β and θ frequencies power during the linguistic tasks; left β/θ and right β/θ EEG power in resting state and during the linguistic tasks; accuracy and reaction times during the linguistic tasks, reading task, and RAN; accuracy in the digit span task). A correction for multiple comparisons will be applied (i.e., the Bonferroni correction). A sample size of 40 was calculated to be enough to achieve a statistical power of 0.87, for medium effect size (η^2^ = 0.06), by setting alpha at 0.05, in the GLMs we planned to carry out to test the effectiveness of the NF intervention.

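### The low-alpha exclusion can be decided from the screening EEG before randomisation, but is written as an approximate exclusion at analysis, with no allowance for it in the 40 enrolled and powered

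*Protocol article*

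**What the plan says.** All references are to the protocol article.

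- **Procedure, the rule.** The screening session records resting EEG and two linguistic tasks. Data from participants with an abnormally low α frequency, "which could potentially make calculations on the β/θ ratio misleading, will be excluded from the analyses". Low is defined as "α peak frequency below about 8.5 Hz at TP during resting-state".
- **Procedure, the order of events.** Eligibility is checked in an online phase against the inclusion and exclusion criteria. The EEG screening session then gives the TP7–TP8 asymmetry in the β/θ ratio, and the 1:1 randomisation is stratified on that score. Every participant then attends the training session.
- **Participants.** "Forty participants will be enrolled in the study". The exclusion criteria cover intellectual disability, psychiatric, neurodevelopmental and neurological conditions, epilepsy and certain university courses. A low α peak is not among them.
- **Data Analyses.** The model for each outcome is "a mixed factorial ANOVA 2 × 2, considering Phase (pre vs. post) and Condition (experimental vs. sham) as the independent variables". On size, the section states: "A sample size of 40 was calculated to be enough to achieve a statistical power of 0.87". The inputs it names are an η² of 0.06 and a significance level of 0.05. No replacement of excluded participants and no inflation of the sample size is mentioned.

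**The concern.** The α peak is measured in the same recording that supplies the stratification score. Whether a participant passes is therefore known, or can be, before anyone is allocated. The plan nevertheless treats the criterion as a reason to leave data out of the analysis and not as a reason not to randomise.

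Three things are at stake.

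1. **Number analysed.** If the 40 enrolled include people with a low α peak who are not replaced, fewer than 40 are analysed, while the power statement rests on 40.
2. **Balance.** Removing people after a stratified 1:1 allocation disturbs the balance that the stratification was meant to secure.
3. **Discretion.** A cut-off of *about* 8.5 Hz *at TP* does not say what happens to a peak just either side of 8.5 Hz, or to one that is low at TP7 but not at TP8. If such cases are settled at analysis, allocation or outcomes may already be known. With about 20 per arm, one or two such decisions can matter.

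**Working it through.** **Timing, from the text.** The sections set side by side:

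| Point | Where | What follows |
|---|---|---|
| α peak read from the screening resting EEG | Procedure | Known before allocation |
| Stratification score from the same session | Procedure; Neurophysiological Measures | Allocation cannot precede this recording |
| Consequence is exclusion from the analyses | Procedure | Worded as an analysis rule |
| Not in the list of exclusion criteria | Participants | Not worded as an eligibility rule |
| Those eligible under the listed criteria are randomised | Procedure | Read literally, low-α participants are included |

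No sentence says outright that low-α participants are, or are not, randomised and trained.

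**Reproducing the stated power.** Inputs from Data Analyses: N = 40, η² = 0.06, α = 0.05, two groups, two measurements (m = 2). Assumption: pre-post correlation ρ = 0.5, which the article does not give.

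- f² = η²/(1 − η²) = 0.06/0.94 = 0.0638, so f = 0.2526.
- For the Phase × Condition interaction, λ = f² × N × m/(1 − ρ) = 0.0638 × 40 × 2/0.5 = 10.21, with 1 and N − 2 = 38 degrees of freedom.
- Power from the noncentral F distribution is 0.876. With the rounded f = 0.25 it is 0.869.

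Both agree with the stated 0.87 to within one point. The result depends on ρ: at N = 40, power would be 0.749 with ρ = 0.3 and 0.936 with ρ = 0.6. The value 0.5 is used because it recovers the article's figure.

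**Fewer analysed, same inputs.** Here λ = 0.2553 × N. The exclusion rate is not given, so the losses are a range and not a forecast.

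| Analysed | Lost from 40 | Power |
|---|---|---|
| 40 | 0 | 0.876 |
| 39 | 2.5% | 0.867 |
| 38 | 5% | 0.858 |
| 36 | 10% | 0.838 |
| 34 | 15% | 0.815 |
| 33 | 17.5% | 0.803 |
| 32 | 20% | 0.790 |

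Forty is the smallest N with power of at least 0.87, so there is no reserve. A single loss gives 0.867, which still rounds to the stated figure; each loss costs roughly one percentage point.

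**Imbalance.** If four are lost, all from one arm (16 against 20), power is 0.833, compared with 0.838 for 18 against 18. For power, the number lost matters far more than the arm it comes from.

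**Keeping 40.** With a share d failing the rule, 40/(1 − d), rounded up, gives 43 for 5%, 45 for 10%, 48 for 15% and 50 for 20%.

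**The case against.** The strongest reply is that the article never says these participants are randomised. The exclusion sentence stands in the description of the screening session, ahead of the stratification. Its stated reason is that a low α peak distorts β/θ calculations, and the stratification score is itself a β/θ calculation. Removal before allocation is therefore a coherent reading. This stands: a reader might infer that the plan commits to exclusions after randomisation, or that people will certainly sit through a session whose data go unused, but the text settles neither.

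A reader might also infer that the rule biases the comparison. The documents do not support that. The criterion is measured before allocation, and if it is applied strictly and blind to allocation it causes no bias. Nothing says that borderline cases will be decided with allocation or outcomes in view; the approximate wording merely fails to prevent it.

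Nor does it follow that fewer than 40 will necessarily be analysed. That needs at least one low-α participant among the 40 who is not replaced, and it is unclear whether *enrolled* is counted before or after the EEG screening. The power loss is also moderate: under the assumptions used, power stays at or above 0.80 down to 33 analysed.

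Finally, peak detection and replacement are details that an article may leave to a fuller document, and their absence is not held against the plan. What remains is what the article itself fixes: an approximate number, placed at the analysis stage although it is available earlier, and one figure of 40 used for both enrolment and power.

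**Conclusion.** The point holds as a weakness in how the rule is fixed, and it should be corrected. The article has the information before randomisation, does not use it as an eligibility criterion, gives only an approximate cut-off without saying which electrode counts, and leaves open whether low-α participants are randomised.

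Its size is moderate. Any enrolled low-α participant who is not replaced takes power below the calculated value at 40: from 0.876 to 0.838 if 10% are lost and to 0.790 if 20% are lost. These figures rest on an assumed pre-post correlation of 0.5 and on illustrative exclusion rates. The other harms, disturbed stratified balance and discretion over borderline cases, cannot be quantified from the document. The weakness does not invalidate the trial.

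**What to change.** 1. List the rule among the exclusion criteria under Participants, and decide it before randomisation.
2. State the cut-off exactly: the article's own 8.5 Hz, without *about*.
3. State the electrode rule. The investigators should choose between TP7, TP8, either or both; the article says only TP.
4. Name the resting EEG of the screening session as the only recording used. Resting EEG is also recorded before and after training, and those recordings should play no part.
5. State that 40 means 40 randomised participants who meet the rule, with no later exclusion on α peak.

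The change is one of wording, plus some extra screening. If 5% to 20% failed the rule, 43 to 50 people would need EEG screening to randomise 40, which is 3 to 10 more. The numbers randomised and trained stay at 40.

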### Behavioral Measures

Behavioral assessment includes three self-report questionnaires for reading problem screening, namely the Revised Adult Dyslexia Checklist (Vinegard, 1994), the Adult Reading Questionnaire (ARQ) (Snowling et al., 2012), and the Adult Reading History Questionnaire (ARHQ) (Lefly and Pennington, 2000). Such questionnaires measure the respondent’s academic achievements, attitude toward school, perceived reading and writing difficulties, reading and writing habits and preferences, time management, and organization problems.

To measure reading, standardized norm-referenced text, word, and pseudo-word reading tasks from the LSC-SUA Battery (Montesano et al., 2020) are used. Participants will be asked to read aloud a text passage and lists of words and pseudo-words. For each reading task, reading speed (i.e., syllable/second) and reading accuracy (i.e., number of errors) will be recorded.

Besides reading, RAN is assessed using the RAN test (De Luca et al., 2005), which was found to be a strong predictor of reading difficulties in older individuals (Cancer and Antonietti, 2018a). In this test, participants are required to sequentially name various visual stimuli (i.e., colored squares, black and white icons, and numbers) presented in 10 × 5 matrices. Naming speed (expressed in seconds) and naming accuracy (expressed in the number of naming errors) are recorded.

Finally, verbal working memory, an ability that is typically impaired in individuals with DD (Toffalini et al., 2017), is assessed using the forward and backward digit span task (Wechsler, 2008).

### Neurophysiological Measures

EEG cortical activity will be recorded using the ProComp5 Infiniti System paired with the BioGraph Infiniti Software (Thought Technology Ltd.) from two active sites placed in TP7 and TP8, according to the International 10–10 system (Nuwer et al., 1998). Two reference electrodes will be placed on the earlobes and two ground electrodes will be placed on the mastoids. The sampling rate will be set at 256 Hz and impedance will be kept below 5 kΩ. Artifact rejection will be performed using both an amplitude threshold (20 μV) and visual inspection.

During the screening session, a measure of hemispheric asymmetry will be calculated by subtracting the right β/θ power ratio from the left β/θ power ratio at TP (i.e., TP7–TP8).

For the NF session, the separate power of the α frequency (8–12 Hz), the δ frequency (1–3 Hz), along with that of the target frequencies (β: 13–21 Hz; θ: 4–8 Hz) and their ratio (β/θ) will be extracted by the BioGraph Infiniti Software and will be considered for the analyses. Pre and post-training EEG recordings will include three phases: (1) resting-state with eyes open for 3 min; (2) a computerized phonological task, in which participants are required to decide whether a list of bi-syllabic word pairs rhymed or not (Spironelli et al., 2006, 2008); and (3) a computerized semantic task, in which participants are required to decide whether bi-syllabic word pairs from a list were semantically related or not. For a detailed description of the linguistic tasks, see Spironelli et al. (2006, 2008). For phases (2) and (3), both response times and accuracy rates will be recorded.

### Neurofeedback Protocol

The NF intervention will consist of three NF sessions using the ProComp5 Infiniti paired with the BioGraph Infiniti Software (Thought Technology Ltd.), specifically: (1) a NF warm-up session of 10 min (NF1); (2) a NF training session of 20 min (NF2); and (3) a NF reinforcement session of 10 min (NF3). The NF training will target cortical β/θ activity in the left TP area (TP7) and β/θ activity in the right TP area (TP8), so to suppress the θ activity and enhance the β activity in the left hemisphere, while suppressing β activity and enhancing the θ activity in the right hemisphere. Rewards thresholds adjust themselves automatically and are maintained in a position where the feedback is given 80% of the time. During NF, participants will be sitting comfortably in a chair to reduce muscle tension, in front of a 27″ monitor. A mini-game (“Bust Big Balloons”) from Zukor’s Carnival feedback videogame (Zukor Interactive) will be used. The reward condition will inform participants of increased left β/θ and decreased right β/θ, through animations and sounds representing successful balloon busting (the balloons will burst sequentially from left to right). The inhibit condition will inform participants of decreased left β/θ and increased right β/θ and will cause a visual distractor to appear on the screen (i.e., flickering lights covering the screen) and the balloon busting will stop. Whenever participants can maintain the amplitude of left EEG β/θ ratio above the threshold while maintaining the amplitude of the right θ/β ratio above the threshold for at least 2 s, feedbacks will be given. During training, separate metrics (i.e., β, θ, and β/θ) for each hemisphere will be recorded; Both left and right β/θ will need to meet the threshold to receive the feedback.

Before the main NF training session, a short warm-up session will be delivered to introduce the task using a simplified feedback mechanism. More precisely, the flickering lights animation will be employed for both reward and inhibit feedbacks. Following the main NF training session, a reinforcing session will be delivered to induce cognitive and neurophysiological changes that will last for the extensive length of both post-training behavioral assessment and EEG recording phases – see for example the protocol by Agnoli et al. (2018) for creative enhancement.

As for the placebo condition, a sham NF training will be delivered by showing to control participants pre-recorded video clips of the game animations for the duration of the NF sessions, following the same procedure of the experimental condition (Egner et al., 2002; Ros et al., 2013; Hosseini et al., 2016; Agnoli et al., 2018). Reward and inhibit feedbacks will correspond to a pre-recorded NF demonstrative session, and therefore will not be related to the actual amplitude variation of the bilateral β/θ ratios.

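### The live reward rule has no muscle-specific criterion, so a β-driven effect at TP7/TP8 could not be attributed to cortex from the listed bands alone; a higher-frequency band from the same recordings is a cheap remedy

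*Protocol article*

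**What the plan says.** All references are to the Protocol article.

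- **Reward rule (Neurofeedback Protocol).** Feedback comes once both ratios have met their limits for 2 s or longer ("Whenever participants can maintain the amplitude of left EEG β/θ ratio above the threshold while maintaining the amplitude of the right θ/β ratio above the" …). Left and right are trained in opposite directions: "so to suppress the θ activity and enhance the β activity in the left hemisphere, while suppressing β activity and enhancing the θ activity in" … (TP8). The inhibit condition is the reverse ratio pattern. Neither condition mentions muscle activity.
- **Threshold (same section).** "Rewards thresholds adjust themselves automatically and are maintained in a position where the feedback is given 80% of the time".
- **Sites and bands (Neurophysiological Measures).** Signals come "from two active sites placed in TP7 and TP8, according to the International 10–10 system", sampled at 256 Hz. The target bands are "β: 13–21 Hz; θ: 4–8 Hz) and their ratio (β/θ) will be extracted by the BioGraph Infiniti Software". δ (1–3 Hz) and α (8–12 Hz) are also listed, and nothing above 21 Hz.
- **Artifact handling (same section).** "Artifact rejection will be performed using both an amplitude threshold (20 μV) and visual inspection". The text does not say whether this acts on the live feedback.
- **Seating (Neurofeedback Protocol).** "participants will be sitting comfortably in a chair to reduce muscle tension".
- **Sham (Neurofeedback Protocol).** The reward and inhibit displays come from a pre-recorded session and "therefore will not be related to the actual amplitude variation of the bilateral β/θ ratios".
- **Outcomes (Data Analyses).** These include left and right β and θ power during the linguistic tasks, and left and right β/θ at rest and during the tasks. Each is tested in a Phase × Condition ANOVA.

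**The concern.** Muscle activity recorded at lateral temporal sites can reach into 13–21 Hz. The article does not say so, and it is taken here as an assumption, although the seating instruction shows that muscle tension was considered. Slight tension on the left adds β power at TP7. Relaxation on the right lowers β power at TP8 and so raises right θ/β. Both changes move the signal in the rewarded direction.

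Only the active arm receives feedback tied to its own signal. The sham therefore controls for the visual experience and the effort, but not for a muscle habit learned through the feedback. The rewarded quantities are also the outcome quantities, at the same two sites. If such a habit carried over into the post-training recording, the interaction that is meant to show a restored temporo-parietal imbalance would have a second explanation.

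**Working it through.** **1. The plan's own figure.** The article gives no amplitude or contamination figure to reproduce. Its one computed design figure, power 0.87 for N = 40 and η² = 0.06, comes out at 0.876 with an assumed pre–post correlation of 0.5. It does not bear on this point.

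**2. Can one-sided tension earn reward?** Left tension alone is not enough, because the right condition must hold at the same time. If 80% is the joint reward rate, each side's condition must hold at least 80% of the time. If it is set per side, the right condition holds about 80% of the time. On either reading the right side usually qualifies, and left tension then decides the reward whenever the left side is the one failing.

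**3. Can it reach the outcome?** In the Procedure section, the reinforcement training (NF3) is phase 6 and the post-training EEG is phase 7, directly afterwards. NF3 is there so that induced changes last through the post-training assessments. Muscle tone could persist by the same route, but it would also have to survive artifact rejection.

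**4. Illustration of size (all amplitudes assumed).** EEG at TP7 has a 1/f spectrum over 1–60 Hz and 5 μV RMS, so its power is 25 μV². Left-sided muscle noise is flat over 13–60 Hz, with none in θ.

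- EEG β power = 25 × ln(21/13)/ln(60) = 25 × 0.480/4.094 = 2.93 μV².
- EEG θ power = 25 × ln(8/4)/ln(60) = 25 × 0.693/4.094 = 4.23 μV².
- Ratio without muscle = 2.93/4.23 = 0.69.
- Muscle at 2 μV adds 2² × 8/47 = 0.68 μV² to β, so the ratio is (2.93 + 0.68)/4.23 = 0.85.
- Muscle at 3 μV adds 3² × 8/47 = 1.53 μV², so the ratio is (2.93 + 1.53)/4.23 = 1.05.

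A simulation of 600 s at 256 Hz under the same model agrees and adds the share of one-second segments that exceed 20 μV:

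| Left muscle RMS (μV) | Left β/θ | Change | Segments over 20 μV |
|---|---|---|---|
| 0 | 0.693 | – | 1.2% |
| 1 | 0.733 | +6% | 2.0% |
| 2 | 0.857 | +24% | 4.5% |
| 3 | 1.051 | +52% | 11.2% |
| 4 | 1.340 | +93% | 33.5% |

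At 2–3 μV, 95.5% to 88.8% of segments pass the amplitude cut. Visual inspection is not modelled.

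**5. What the cut sees.** The cut acts on the whole signal, not on 13–21 Hz alone. Muscle of 1.0–1.5 μV RMS within that 8 Hz band corresponds to × √(47/8) = 2.4–3.6 μV over 13–60 Hz. Combined with the EEG, 4 SD is 4 × √(25 + 2.4²) ≈ 22 μV to 4 × √(25 + 3.6²) ≈ 25 μV. Peaks do reach the cut, but most segments stay under it.

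**The case against.** A reader might infer that the protocol has no check on muscle at all. The document does not support that: it states an amplitude cut, visual inspection and seating chosen to limit tension. Together these would remove gross muscle activity from the analysed recordings.

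A reader might also infer that the relevant muscle activity lies far below 20 μV and always escapes. Step 5 of the working shows otherwise, and stronger tension is flagged increasingly often.

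Four further objections have weight.

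- **Length of the causal chain.** The strategy must be learned in 40 minutes of training (10 + 20 + 10), satisfy both sides at once, persist into a separate recording and survive rejection. The self-adjusting threshold also means that sustained tension raises the bar and does not keep earning more reward. This lowers the likelihood but does not remove the mechanism.
- **Separate β and θ analyses.** The Data Analyses and Discussion sections plan these. Muscle power added in 13–21 Hz could not produce an effect driven by θ, so the analyses narrow the problem to β-driven effects. They cannot tell whether a β change is neural.
- **Recoverability.** The listed bands are those to be extracted, not a stated limit on what is stored. If the underlying signal is kept, the pre/post check can be added later, and only the live inhibit must be settled before training.
- **Condensation.** Software inhibit settings may sit in a fuller document, so silence does not prove that there are none. But the article does state its reward rule, inhibit rule, bands and artifact method, and the suggestion improves on that stated method.

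**Conclusion.** The point holds as a cheap improvement to the stated method. No muscle-specific criterion is described for live feedback, and the general artifact handling is not stated to act there. It may leave low-amplitude muscle activity in the β outcomes. Because sham feedback does not depend on the participant's signal, any muscle strategy learned from the feedback would fall in the active arm only. A β-driven Phase × Condition effect could therefore not be attributed to cortex from the listed bands alone.

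The size of any bias is unknown. The 24–52% range rests wholly on assumed EEG and muscle amplitudes, an assumed flat muscle spectrum with nothing in θ, and no visual inspection. It shows that the mechanism is possible, and it is not an estimate for this trial. A reader might go on to infer that a positive result would be muscular. The document does not support that either; it leaves the source of a β change undetermined.

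**What to change.** 1. **Extract a muscle-sensitive band above β** (for example 30–45 Hz) from the existing TP7 and TP8 recordings. Sampling at 256 Hz allows this without new electrodes. Report its power by arm, side and phase.
2. **Fix a rejection limit in advance** for the pre and post epochs. Set it from matched pre-training recordings (rest for rest, task for task) and apply it blind to arm. Repeat the β and β/θ comparisons on the retained epochs as a sensitivity analysis.
3. **Treat any adjustment for change in muscle-band power as sensitivity only**, since that change arises after randomisation.
4. **Where the software allows, add a muscle-band inhibit to the live reward rule.** Set its limit high in the participant's baseline distribution and not at the average, so that the 80% reward schedule is largely kept.

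The cost is a software setting, a small extra analysis, some lost epochs and brief pauses in feedback. The number of epochs rejected should be shown by arm, because unequal loss would itself need explaining.
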